### Intervention

After screening and baseline questionnaires, participants will be randomized using a web-based blocked randomization list of 4, 6, or 8 block sizes and a 1:1 allocation ratio. The intervention group will be instructed to download the Sphygmo BP app via a link provided within the Trial My App. The control group will receive a link to the Heart and Stroke foundation website, which includes information on hypertension management and measuring blood pressure [29]. All participants are expected to continue to receive usual care by their physician, including any anti-hypertensive medication and lifestyle changes.

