## Methods

### Overview

We have developed an innovative research approach using a web-based platform called Trial My App, which is designed to perform efficient trials of apps relevant to patients with cardiovascular risk factors. In our initial phase, we engaged an advisory board of patients to codevelop criteria for app and trial outcome selection, which will be used to support further deployment of Trial My App. The patients used apps for goal setting, decision-making, information sharing, and empowerment in managing their health. From these themes, we derived a series of survey questions to determine if an app was meeting these outcomes, and we included this survey in the pilot trial. Content analysis by the advisory board also indicated that patients considered a number of favorable technical factors when selecting their mobile apps: (1) relevant feedback on progress, (2) security, (3) low cost, (4) customizability, (5) usability, (6) information credibility, (7) multifunctional app integration, and (8) interdevice compatibility. The undesired features were as follows: (1) unreliable technology, (2) distraction, (3) collection of personal information, and (4) learning curve. These criteria were applied to shortlist apps for hypertension, and through discussion with the research team and patient partners, we identified Sphygmo BP as the intervention app for this pilot trial (Multimedia Appendix 1). Sphygmo BP was created in partnership with the University of Alberta to help patients with hypertension to self-manage their blood pressure. The app tracks and averages blood pressure, glucose levels, weight, temperature, respiratory rate, and oxygen saturation. It also includes educational components to facilitate better patient awareness of management strategies for blood pressure and is designed to facilitate patient-physician communication through telemonitoring.

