All trial stages, including screening, consent, randomization, and collection of clinical and patient-important outcomes data, will be performed virtually using the Trial My App platform. This phase includes a substudy to validate the web-based collection of patient data. Ethics approval of the substudy will be sought separately. Participants will be asked to register on the Trial My App site with an email and a password. The informed consent form is in Multimedia Appendix 2. Once they have electronically consented to using the web app, they will complete a user profile questionnaire and be screened for participation in the pilot trial in a subsequent survey. Multimedia Appendix 3 contains all user baseline, screening, and follow-up questionnaires. If participants meet inclusion criteria, they will be asked to electronically consent to take part in the pilot trial and provide data at 0, 1, 3, and 6 months. The participant flow is shown in Figure 1. The diagram of the app flow is shown in Figure 2.

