**Clinical assessment**		
	Difference in mean change in blood pressure from baseline to 6 months between groups	Statistically significant difference in mean change in systolic blood pressure measurements (defined as *P*<.05 using a Pearson test)
	Proportion of patients at their recommended blood pressure	Blood pressure measurements compared to standard ranges

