## Appendix

Multimedia Appendix 1 Description of the blood pressure management app used for the study.

Multimedia Appendix 2 Information and consent form.

Multimedia Appendix 3 Study instruments.

Multimedia Appendix 4 Peer review report.

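### Guidance on measuring blood pressure is named only in the control arm's website link, sent after baseline, so a measurement effect that differs by arm is possible

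*Protocol article*

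**What the plan says.** The Intervention section fixes the order of events: "After screening and baseline questionnaires, participants will be randomized". Assigned material therefore reaches participants after the baseline reading has been entered.

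The same section describes what each arm then gets:

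- Control: "The control group will receive a link to the Heart and Stroke foundation website, which includes information on hypertension management and measuring blood pressure".
- App: "The intervention group will be instructed to download the Sphygmo BP app via a link provided within the Trial My App". Nothing is said there about how to take a reading.

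The Overview says that the app tracks and averages blood pressure, supports telemonitoring and has "educational components to facilitate better patient awareness of management strategies for blood pressure". Measuring technique is neither mentioned nor excluded.

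The first clinical outcome in Table 2 is "Difference in mean change in blood pressure from baseline to 6 months between groups". The text on pilot efficacy outcomes says the values are self-reported in the questionnaires. The Eligibility Criteria accept any device the participant can reach, at home or in the community.

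Two sources that bear on this were not available for this review. The Appendix lists "Multimedia Appendix 1 Description of the blood pressure management app used for the study", and the Recruitment section says "Multimedia Appendix 3 contains all user baseline, screening, and follow-up questionnaires".

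**The concern.** An education control may differ from the app in what it teaches about managing hypertension; that is the contrast set out under Objectives. Guidance on taking the reading is another matter, because it can move the recorded number while true pressure stays the same.

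As the article describes it, the control arm's change runs from a reading with no stated guidance to one taken after guidance was offered. The app arm's change is not described that way. Randomisation does not balance this, because the difference arises after allocation.

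If the guidance lowers control readings, the app's benefit is understated. If it raises them, the benefit is overstated. The planned comparison cannot separate either shift from an effect of the app. The Sample Size section intends to tell patients and physicians, if a difference is found, that the app may have a major effect on clinical outcomes, so a distorted difference would matter.

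**Working it through.** **Reproducing the plan's figure.** The inputs, from the Sample Size section, are a difference of 8 mm Hg, SD 18 mm Hg, 80% power and 5% type I error (two-sided assumed; sidedness is not stated).

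n per arm = 2 × 18² × (1.96 + 0.8416)² / 8² = 79.5, so 80. The t-based calculation gives 79.8% power at 80 per arm and 80.3% at 81, so the plan's 81 is reproduced. With 20% dropout, 80 / 0.8 = 100 per arm, as stated.

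**Illustrating a control-only shift.** Take 80 analysed per arm (100 less 20%).

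SE = 18 × √(2/80) = 2.846 mm Hg.

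Let b be the average lowering of control readings, net of any measurement effect in the app arm and taken over all analysed controls, including those who never open the link. The documents give no value for b; the values below are assumptions. A true 8 mm Hg benefit then appears as 8 − b, and power ≈ Φ((8 − b)/2.846 − 1.96).

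| Assumed b (mm Hg) | Apparent benefit (mm Hg) | Power |
|---|---|---|
| −3 (controls read higher) | 11 | 97% |
| −2 | 10 | 94% |
| −1 | 9 | 89% |
| 0 | 8 | 80% |
| 1 (controls read lower) | 7 | 69% |
| 2 | 6 | 56% |
| 3 | 5 | 42% |
| 4 | 4 | 29% |

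**With no true effect.** The two-sided rejection rate is Φ(|b|/2.846 − 1.96) + Φ(−|b|/2.846 − 1.96). For |b| = 2 this is Φ(−1.257) + Φ(−2.663) = 0.104 + 0.004 = 0.108. For |b| = 1 it is 0.064, and for |b| = 3 it is 0.184. The nominal rate is 0.05.

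These figures show what a bias of a given size would do. They do not show that a bias exists.

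**The case against.** The strongest reply is that the point leans on silence. The appendix on the app may show that it teaches measuring technique. The questionnaires may carry measuring instructions for everyone, at baseline as well as later. A journal article commonly leaves such detail to its appendices. This stands, and it limits the point to what the article names and when that material is delivered.

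A reader might go further and infer that controls alone are instructed, that baseline readings are uninstructed, and that the control arm's change therefore contains a technique effect. The documents do not support that:

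- Nothing says that the app arm gets no measuring guidance, or that baseline readings are taken without any.
- A link may go unread, and a page that is read may not change technique.
- The app tracks and averages readings, so it may affect recorded values too. Even the direction of a net difference is open.

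It can also be said that the website is the declared comparator, that blood pressure is a secondary objective of a pilot, and that the Sample Size section offers its power calculation as a guide to recruitment. All of this is true and lowers the stakes. It does not answer why guidance on taking the outcome measurement should be named in one arm only.

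The Discussion acknowledges measurement error in self-report and plans a concordance substudy against 7-day home averages (40 participants, per the Abstract). As described, that substudy neither compares concordance between arms nor corrects the trial estimate.

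**Conclusion.** The point holds as a possible differential measurement bias in the main efficacy outcome; it does not touch the primary feasibility outcome. The article names measuring guidance only in the control link, places that link after the baseline reading, and states no guidance common to both arms. Combined with a change-from-baseline endpoint based on self-reported readings from unstandardised devices, that leaves room for a measurement effect that differs by arm.

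Neither its size nor its direction can be taken from the documents. The loss of power from about 80% to 56%, and the rise in false rejection from 5% to about 11%, both rest on an assumed net shift of 2 mm Hg, SD 18 mm Hg, 80 analysed per arm and a two-sided test. If the questionnaires already give everyone the same measuring instructions before baseline, the remedy is largely in place and the article need only say so.

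**What to change.** Show one identical block of guidance on measuring blood pressure to every participant inside Trial My App before the baseline value is entered, and repeat it in the 1, 3 and 6 month questionnaires. The website's own measuring page would serve. If the questionnaires already contain this, state it in the Intervention or Data Collection section.

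The contrast under Objectives, app against website, is kept. The cost is a link or text block on existing questionnaires. The downside is that both arms receive slightly more instruction than usual care would give, but equally.

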### Data Collection

At 1, 3, and 6 months after enrollment into the RCT, Trial My App will send email reminders with a link to follow-up questionnaires to all participants to assess self-reported blood pressure and several patient-reported outcomes. Completing follow-up will be defined as answering the questionnaire within 7 days of receipt of the questionnaire notification via email. To encourage participation and reduce attrition, participants will receive a Can $10 (US $1=Can $1.27) electronic gift card for each completed assessment and an additional Can $10 gift card if they complete all 4 follow-up assessments.

### Outcomes

#### Feasibility Outcomes

Our primary goal at this stage is to determine whether the Trial My App platform can be used to conduct RCTs evaluating mHealth apps by the ability to complete an adequately powered RCT of least 80 participants in each group that successfully complete the study and the 6-month questionnaire within an arbitrarily defined reasonable time frame of 12 months. The remaining feasibility outcomes and associated indicators are shown in Table 1.

**Table 1 table1:** Feasibility outcomes and indicators.

Outcome	Definition	Indicator	Minimum required sample size
Participation completion	Number of participants who successfully complete the final questionnaire within 1 year of trial start	80% out of total randomized participants in each group	100 participants per group is needed to achieve a margin of error of 8% with a 95% confidence level
Eligibility	Proportion of participants who sign up that meet eligibility criteria	At least 50% of responses to baseline and screening questionnaires are eligible	200 participants in total to achieve a margin of error of 7% with a 95% CI
Recruitment	Number of eligible participants recruited and consented	At least 50% of target sample size of 200 randomized within 6 months	200 participants in total to achieve a margin of error of 7% with a 95% CI
Retention	Proportion of withdrawal and dropouts after recruitment	Less than 20% of the participants lost to 6-month follow-up	200 participants in total to achieve a margin of error of 5.5% with a 95% CI
Outcome acceptability	Follow-up questionnaire completion rates	70% of the questionnaires that are submitted within 7 days of notification reminder	200 participants in total to achieve a margin of error of 6.3% with a 95% CI
Intervention acceptability	Frequency of app usage in the intervention group	Answers to frequency of use and features used questions in follow-up questionnaires	N/A^a^
Appropriateness of data collection processes	Completeness of data	50% of the questionnaires completed and less than 20% of the missing response rates in each questionnaire	N/A

^a^N/A: not applicable.

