### Sample Size

In the feasibility study, at least 80% of the participants in each group who successfully complete the final questionnaire within 1 year of trial start will be considered as the primary feasibility outcome. To estimate a completion rate of 80% in each group within a margin of error of 8% and with a confidence interval of 95%, we estimated a sample size of at least 100 participants in each group, and 200 participants in total is required. With a sample size of 200 participants in total (ie, 100 per group), we will have 80% power to detect a reduction in blood pressure of 8 mm Hg, which is considered a minimally clinically important difference. Assuming an 18 mm Hg standard deviation in systolic blood pressure, to detect an 8 mm Hg difference between groups with a power of 80% and a type I error of 5%, we would ideally require 81 participants in each arm [28]. Accounting for a 20% dropout rate, we aim to enroll 100 participants in each arm. We recognize that the selected app may not result in such a large difference in the systolic blood pressure, but the calculation is to guide our recruitment targets. If a difference in the blood pressure is found, we will be able to inform patients and physicians that this app may have a major impact on clinical outcomes such as heart attack, stroke, and congestive heart failure. 

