## Results

### Trial Progress

The development of the Trial My App web platform has been completed with a software developer and has undergone functionality and remote usability testing to uncover technical bugs and improve the design. The creation of survey instruments has been completed in collaboration with our patient partners and advisory board. Recruitment is expected to begin in the first quarter of 2021; data collection and analysis are expected to be completed approximately 1 year after study commencement. Dissemination of results will occur through conferences and publications.

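### The Table 1 recruitment mark (100 of 200 randomised by month 6) is too low for the primary feasibility criterion of 80 completers per group within 12 months of trial start

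*Protocol article*

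**What the plan says.** Three statements in the protocol article bear on this point.

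- **Recruitment.** The indicator in Table 1 (Feasibility Outcomes) is "At least 50% of target sample size of 200 randomized within 6 months".
- **Primary feasibility outcome.** The text of Feasibility Outcomes asks for an "adequately powered RCT of least 80 participants in each group that successfully complete the study and the 6-month questionnaire", to be achieved "within an arbitrarily defined reasonable time frame of 12 months". The participation completion row of Table 1 defines the outcome as "Number of participants who successfully complete the final questionnaire within 1 year of trial start", with the indicator "80% out of total randomized participants in each group". Sample Size also uses the percentage: "at least 80% of the participants in each group who successfully complete the final questionnaire within 1 year of trial start". So there is a count version (80 per group) and a percentage version (80% of those randomised per group).
- **Follow-up.** Under Data Collection, questionnaires go out 1, 3 and 6 months after enrolment, and each must be answered within 7 days of its notification.

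Trial Progress adds that "data collection and analysis are expected to be completed approximately 1 year after study commencement". Sample Size plans 100 per group with 20% dropout, and the Intervention section gives 1:1 blocked randomisation.

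**The concern.** The primary criterion runs on a calendar clock that starts with the trial, while follow-up runs from each participant's own enrolment. The last randomisation that can contribute a completer is therefore at about month 6, which is also when recruitment is judged. The month-6 recruitment count is thus a ceiling on the number of timely completers, and a mark of 100 puts that ceiling well below the 160 (2 × 80) that the count version needs.

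In a feasibility trial these indicators are the main result. A recruitment row that reports success when the primary outcome is already out of reach gives no useful signal. The retention row of Table 1 has no trial-start clock, so a trial could pass recruitment and retention and still fail its primary outcome on the calendar alone.

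**Working it through.** **The plan's own figures reproduce.**
- Blood pressure: SD 18, difference 8, power 80%, 5% type I error (two-sided assumed, as sidedness is not stated). n per group = 2 × [18 × (1.960 + 0.842) / 8]² = 79.5 by the normal approximation and 80.4 by the t-test. The stated 81 is right.
- Dropout: 80 / 0.8 = 100 and 81 / 0.8 = 101.3, so 100 per group is close enough.
- Completion margin of error: 1.96 × √(0.8 × 0.2 / 100) = 7.8%, stated as 8%.

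The sample size is not in question. What follows concerns the timetable.

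**Latest randomisation that can count.** 12 − 6 = month 6. If the full 7-day response window is to fall inside the limit, it is about a week earlier.

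**Count version.** With R randomised by month 6, 1:1 allocation and loss d, timely completers per group are at most (R / 2) × (1 − d). An unfinished block of up to 8 can shift the split by a few.

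| Randomised by month 6 | Per group | No loss | 10% loss | 20% loss |
|---|---|---|---|---|
| 100 (the mark) | 50 | 50 | 45 | 40 |
| 120 | 60 | 60 | 54 | 48 |
| 160 | 80 | 80 | 72 | 64 |
| 180 | 90 | 90 | 81 | 72 |
| 200 | 100 | 100 | 90 | 80 |

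Turned round, the month-6 total needed for 80 per group is 2 × 80 / (1 − d), with each group rounded up:
- no loss: 160
- 5% loss: 2 × 85 = 170
- 10% loss: 2 × 89 = 178
- 15% loss: 2 × 95 = 190
- 20% loss: 200

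Every total from 100 to 159 passes recruitment and cannot give 80 per group.

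**Percentage version.** At the mark, 50 per group can complete in time with no loss.
- If enrolment continues to the planned 100 per group, the rate is at most 50 / 100 = 50%, or 40 / 100 = 40% at 20% loss.
- 80% stays reachable only while the total randomised is at most 100 / 0.8 = 125 (no loss), or 80 / 0.8 = 100 (20% loss).
- Stopping at 100 with 40 of 50 per group would meet the percentage, but would miss the 80-per-group count and the planned size.

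**Timetable at the mark's pace.** Assume constant accrual of 100 per 6 months, 16.7 a month. The 160th participant is randomised at 160 / 16.7 = month 9.6 and the 200th at month 12. Their final questionnaires fall at months 15.6 and 18.

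**Power.** Under the same assumptions, power for 8 mm Hg is about 60% with 50 per group and about 51% with 40. A trial with only those timely completers would not have the 80% power that the plan sets out.

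**The case against.** A reader might infer that the recruitment mark and the primary criterion contradict each other outright. The documents do not support that. The mark is worded as a minimum, and a trial with 160 to 200 randomised by month 6 can pass both. Nothing says that passing recruitment implies passing completion, and no progression rule links the two rows. Passing a lenient indicator and failing a stricter one is not in itself a contradiction.

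A reader might also infer that all 200 must be randomised by month 6. That holds only at exactly 20% loss. Table 1 aims for less than 20%, and at 10% loss 178 suffice.

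Third, it is tempting to call it a flaw that the primary outcome mixes recruitment speed with completion. The plan does this on purpose: it asks whether participants can "successfully complete the study and the 6-month questionnaire within an arbitrarily defined reasonable time frame of 12 months", and rapid evaluation is the reason for the platform. A platform with good retention and slow accrual is meant to fail. Recruitment and retention have their own rows, so the cause of a failure would be visible.

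Finally, the percentage version fails at the mark only if enrolment runs on past about 125. The one-year schedule in Trial Progress implies little or no enrolment after month 6, so late enrolment would mean that the schedule had already slipped.

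These points limit the size of the problem. They leave standing that the month-6 mark is set at 100 when the criterion it should foreshadow needs at least 160.

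**Conclusion.** The recruitment indicator is too low to be consistent with the primary feasibility criterion. It falls short by 60 participants with no loss (160 against 100) and by 100 at the planned 20% loss (200 against 100). The percentage version is also unreachable at the mark if enrolment continues towards 200.

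The conclusion assumes that trial start is a single calendar date for the whole study, which the Table 1 wording and the one-year schedule in Trial Progress both support. If the 12 months ran from each participant's own enrolment the conflict would vanish, but that is not what is written. It also assumes close to equal allocation at month 6.

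This is a should-fix. The mismatch does not bias the blood pressure comparison, and the components are reported separately. It does leave a stated success threshold that gives no warning when the primary outcome is already lost.

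**What to change.** Keep the 12-month criterion and raise the recruitment indicator in Table 1 to the number that it requires by month 6, less the 7-day response window. That number is 160 if no loss is assumed, 178 at 10% loss and 200 at the planned 20%. State which loss rate the chosen figure assumes.

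Alternatively, if slower recruitment is acceptable, keep the 50% mark and restate the 12-month limit and the study duration, which would be about 18 months at 100 per 6 months. This relaxes the stated speed objective, and the protocol should say so.

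In either case, state whether success means 80 completers per group or 80% of those randomised. The two agree only at 100 per group.

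The first option costs one table entry and a sentence. The second also changes the primary outcome's time limit, the Sample Size wording and the stated timeline. Neither changes the sample size or the data collected.
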